
**15.6. Will recordings be obtained in this research study?**

☒ **No** ☐ **Yes:** *If yes, select the kind(s) of recording and describe the transcription and destruction plan.*

☐ Audio recording

☐ Video recording

Transcription plan: Interviews may be recorded for quality control purposes by IPA. Respondents are free to refuse audio recording with no consequences. These recordings will not be transcribed or shared with the research team.

Destruction plan: Audio recordings will be destroyed after completion of audio audits.

**15.7. Indicate who is responsible for data/specimen management and how the research team and/or other collaborators are permitted access to information.**

IPA is responsible to put in place the data protection systems outlined, then will share permissions with the team of primary researchers who will jointly manage the data on Harvard Dropbox. To access the information, the researchers must log into Harvard Dropbox on their computer or online. Any collaborators would also have to log into the cloud to access the dataset.

**15.8. Indicate how long data/specimens will be stored and describe the plans at the end of the storage period (e.g., are data/specimens destroyed, returned to data/specimen provider, etc.).**

All books, records and reports will be kept for five years following the end of the study period.

**16. Data/Statistical Analyses Plan**

**16.1. Describe plans for analysis (including the statistical method, if applicable).**

Statistical analysis will consist of summarizing data with descriptive statistics and t-tests, and evaluating the effectiveness of the intervention using multiple regression.

**16.2. Is there a sample size/power calculation?**

☐ No ☒ Yes: *If yes, describe the calculation and the scientific rationale, and, if applicable, by site and key characteristics such as participant demographics.*

The baseline sample size is based on the power calculation for postnatal care within 6 weeks of delivery, which is our primary outcome for patient care seeking. Based on Jacaranda's internal data, we assume that 61% of women will receive any postnatal care visit within 6-8 weeks of delivery in the absence of the intervention. Based on health information system volume data, we would expect to see 120 ANC patients new to the intervention in study facilities in a given month and we expect at least 80% of them will be enrolled into the PROMPTS intervention. We plan to enroll women over at least a one-month period to reach this target. Assuming that we can track 75% of these women postpartum regarding post-delivery outcomes, we would expect to follow roughly 58 women for this outcome in each facility. Assuming an ICC of 0.01, the minimum detectable impact is an increase in postnatal care receipt of 7 percentage points or a 11% increase in postnatal care seeking.

The endline sample size is based on the power calculation for quality of care during labor, delivery and immediate postpartum, which is our primary health worker outcome. We assume that we will be able to observe at least 100 complete deliveries during six weeks of observation in each facility at the endline. Based on the PIs recent work in Uganda and Kenya, which used a very similar technique of clinical observations of deliveries in similar health facilities, we assume that average quality of care for the control group will be 0.58 (i.e., health workers will perform just over half of the important aspects of quality of care) with a standard deviation of 0.13. Assuming an intra-cluster correlation (ICC) of 0.35 (based on baseline data from our previous work), a cluster size of 100 patients, 20 clusters per arm, alpha of 0.05, and power of 0.80, the minimum detectable impact would be 6.88 percentage point increase in quality of care or an 11.9% increase in the quality-of-care index.

**17. Costs and Compensation** ☐ N/A. *Skip to next section.*

**17.1. Identify any costs that participants may incur during the study, including transportation costs, childcare, or other out-of-pocket expenses.**

There are no other anticipated costs that participants may incur during the study.

**17.2. Identify remuneration that participants may receive during the study. Specify the amount, timing of disbursement, and method (e.g. money, gift cards, in-kind, incentives, raffles, and transportation). Describe how compensation will be calculated and paid if a participant withdraws. If any participant will receive a single payment more than \$100, or \$600 or more in one calendar year, refer to [Harvard University Financial Policy on Human Subject Payments](#).**

Facilities will be given a small gift (such as a clock or infrared thermometers) for participation in the study. All participating facilities will receive the same gift with the value around KES 3500.

Health workers will be offered a small token of appreciation in the form of airtime with the value of around KES 200 for participating in the health worker surveys.

Women recruited from the ANC clinic will receive a small token of appreciation in the form of airtime with the value of KES 100 per survey (baseline survey and two follow-up calls).

**18. Sharing Study Results** ☒ N/A. *Skip to next section.*

**18.1. Describe the plan to share study results with individual participants, the participant group/community, and/or others.**

We plan to share a report of the findings with directors of health, department of family health, leadership of other counties, and facilities through technical working groups.

**19. Research Related Injuries** ☐ N/A. *Skip to next section.*

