## 5. Study Design

### 5.1. Describe the study design type.

This study is designed as a parallel arm cluster randomized control trial (RCT). Randomization of the intervention package will occur at the facility level. Overall, 40 - 50 facilities across 8 - 10 counties will be randomized into either the intervention or control group. Facilities will be chosen to ensure sufficient geographical distance from all other facilities included in the sample.

Data will be collected at multiple points during the study period (see the table below). The baseline data collection period will last for about a month in each facility. Baseline data collection will include facility assessment, register data extraction, and health worker interviews. The MENTORS program will be rolled out in intervention facilities after the baseline data collection.

The facility-based endline data collection will occur 4-5 months after the end of baseline and will last for 1-2 months in each facility. The facility-based endline data collection will include register data extraction, health worker interviews, and observations of quality of care during labor and delivery.

Process evaluation includes extraction of administrative program data collected by Jacaranda Health to monitor intervention implementation. Jacaranda Health will share this data with us throughout the study period.

We will recruit pregnant women from antenatal care clinics during the baseline data collection period. For this sample, we will conduct two follow-up surveys by phone—one towards the end of pregnancy and another at around 7- to 8-weeks postpartum. Women enrolled from the intervention facilities will be offered the PROMPTS intervention immediately after the baseline survey.

After the endline, facilities in the control group will also receive the intervention package.

In summary, we plan to collect the following data:

|                          | Facility-Based Data Collection |                   |                | Phone Surveys with Pregnant Women Cohort |                                 |
|--------------------------|---------------------------------------|-------------------|----------------|-------------------------------------------------|---------------------------------|
|                          | Baseline                       | In-between | Endline | End of pregnancy                         | 7- to 8-weeks postpartum |

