- 1) The enumerator will approach all health workers that meet the inclusion criteria at the maternity ward. The enumerator will approach health workers individually, share with them the purpose of the interview, and ask whether they are willing to participate.
- 2) The enumerator will schedule an interview with each health worker at a time when the staff is not busy with other duties.
- 3) The enumerator will meet each health worker at the scheduled time. The enumerator will identify a quiet and private space where the enumerator and the health worker will sit together for the duration of the interview. The enumerator will ask the required information and ask the staff member any clarifying questions. Each respondent will be interviewed individually and privately, and preferably outdoors. The interviews may be recorded for quality control purposes.

**Patient interviews with a cohort of pregnant women:** we will recruit pregnant women who visit health facilities for antenatal care. One or two enumerators will be stationed outside of the antenatal care clinic in each facility to enroll prenatal patients. Pregnant women who consent to participate in the study will be contacted by phone toward the end of their pregnancy and at about 7 – 8 weeks postpartum for follow-up surveys. Women from intervention facilities who agree to receiving text messages will be enrolled in the PROMPTS program by Jacaranda Health. Procedures for data collection are as follows:

- 1) The enumerators will be on site before the antenatal care clinic is open to see patients.
- 2) Enumerators will approach women before or after they receive antenatal care (e.g., to wait for her providers or right after the completion of her visit) and recruit them to participate in the study. Enumerators will obtain women's consent and conduct a short survey on health care utilization, knowledge, and demographics (including women's contact information for follow-up calls). This will be done in a private space to protect participants' privacy and preferably outdoors. If the respondent does not have a mask, the enumerator will provide one.
- 3) Enumerators will also make a short announcement periodically to those in the waiting bay/queue that they are recruiting participants for a research study and can explain the details of the study for those interested outdoors.

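### Section 16.2 uses PROMPTS uptake, which occurs in one arm only, to reduce the women followed in every facility; this conflicts with sections 5.4 and 5.7, and the stated 58 does not follow from its own inputs

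*Protocol*

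**What the plan says.** Section 16.2 (sample size) builds the postnatal-care calculation in steps:

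- Control rate: "we assume that 61% of women will receive any postnatal care visit within 6-8 weeks of delivery in the absence of the intervention".
- Volume: "we would expect to see 120 ANC patients new to the intervention in study facilities in a given month".
- Uptake: "we expect at least 80% of them will be enrolled into the PROMPTS intervention".
- Tracking: "Assuming that we can track 75% of these women postpartum regarding post-delivery outcomes".
- Result: "we would expect to follow roughly 58 women for this outcome in each facility".

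With an ICC of 0.01 it then gives a minimum detectable increase of 7 percentage points, or 11%.

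The design and procedures sections describe a different cohort. Section 5.4 plans about 4800 antenatal women, about 120 per facility. Section 5.7 ties follow-up to study consent alone: "Pregnant women who consent to participate in the study will be contacted by phone toward the end of their pregnancy", and again at about 7 to 8 weeks postpartum. PROMPTS is a separate step in one arm: "Women from intervention facilities who agree to receiving text messages will be enrolled in the PROMPTS program by Jacaranda Health". Section 5.1 gives its timing: "Women enrolled from the intervention facilities will be offered the PROMPTS intervention immediately after the baseline survey". Randomization is by facility (section 5.1).

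**The concern.** The women tracked in section 16.2 are, as the sentence reads, those enrolled in PROMPTS. Control facilities have no such women during the study, yet the resulting count is applied to every facility. The count therefore describes neither the control arm nor the cohort that sections 5.4 and 5.7 set up.

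Uptake is also put in the wrong place. When facilities are randomized and all consented women are followed, a woman who declines the texts still contributes an outcome. Declining lowers the average effect in the intervention arm; it does not remove her from the denominator. Treating uptake as a loss of numbers makes the sample too small and leaves open whether the 7 points is the difference between arms or the effect among users. Postnatal care is the primary outcome for patient care seeking, so the protocol should show what the planned cohort can detect.

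**Working it through.** **Inputs.** From section 16.2: control rate 0.61; 120 women per facility; uptake 0.80 (stated as a minimum); tracking 0.75; ICC 0.01. From section 5.4: about 120 women enrolled per facility. Cluster number, alpha and power are not given for this outcome. I assume that 20 facilities per arm, alpha 0.05 and power 0.80 carry over from the quality-of-care calculation in the same section, and that the test is two-sided.

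**Formulas.** Let m be the women followed per facility.

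- Design effect: DE = 1 + (m − 1) × 0.01.
- Effective number per arm: n = 20m / DE.
- Power for a difference d: Φ[(d − 1.96 × se0) / se1]. Here se0 = √(2 p̄(1 − p̄)/n), with p̄ the mean of the two rates, and se1 = √([p1(1 − p1) + p2(1 − p2)]/n).
- The MDE is the d that gives 80% power.

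**Step 1: the plan's own figure.** With m = 58, DE = 1.57 and n = 1160/1.57 = 739. At d = 0.07, se0 = 0.0249 and se1 = 0.0248, so power = Φ(0.854) = 80.3%. The MDE is 6.97 points, and 7/61 = 11.5%. The 7 points reproduces from 58 women.

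**Step 2: the 58.** The stated chain is 120 × 0.80 × 0.75 = 72. Reaching 58 takes a second factor of 0.80 that the text does not state: 120 × 0.80 × 0.80 × 0.75 = 57.6.

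**Step 3: the cohort in sections 5.4 and 5.7.** With no uptake filter, 120 × 0.75 = 90.

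| Women followed per facility | DE | n per arm | MDE, as randomized | Power at 7 points, as randomized |
|---|---|---|---|---|
| 58 (stated) | 1.57 | 739 | 7.0 points | 80% |
| 72 (stated factors) | 1.71 | 842 | 6.5 points | 85% |
| 90 (all consented, 75% tracked) | 1.89 | 952 | 6.2 points | 89% |

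**Step 4: uptake placed on the effect.** Assume that non-acceptors gain nothing. The difference between arms is then uptake × effect among users.

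- At 80% uptake, the 6.16-point MDE corresponds to 6.16/0.80 = 7.7 points among users.
- A 7-point effect among users becomes 0.80 × 7 = 5.6 points. With m = 90, se0 = se1 = 0.0220 and power = Φ(0.584) = 72%.
- With m = 90 and 7 points among users, power is 60% at 70% uptake, 72% at 80% and 82% at 90%. It reaches 80% at about 88% uptake.

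**Sensitivity.** Using a t reference with 38 degrees of freedom, the MDE at 90 women is 6.3 points. Section 5.1 allows 40 to 50 facilities; at 25 per arm the MDE at 90 women is 5.5 points.

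**The case against.** The strongest defence is that this is loose sample-size text with no harm to the trial. The operational sections enrol and telephone all consenting women, randomization is by facility, and the stated aim is the effect of the package. If 7 points means the difference between arms, following 90 women instead of 58 helps: power is 89% and the stated MDE is conservative. The definition of the analysis population may sit in an analysis plan that is not shown. All of that stands. It limits the consequence but does not remove the inconsistency in section 16.2.

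Three stronger readings are tempting, and the protocol does not support them.

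- *The trial will compare acceptors with all control women, so it is biased.* Nothing in the protocol restricts the analysis to acceptors. If it did, and acceptors' untreated rate exceeded decliners' by 5 to 20 points (an assumption), the bias at 80% uptake would be 0.20 × gap, or 1 to 4 points. That applies only to an analysis the protocol does not plan.
- *The trial is underpowered, at 61%.* That figure pairs 58 women with a 5.6-point effect. It charges non-uptake once in the count and again in the effect. With all consented women followed, the matching figure is 72%. Even that requires 7 points to be the effect among users, no benefit in non-acceptors (whose facilities also receive MENTORS), and uptake below about 88%, when the text says at least 80%.
- *Enumerators recruit knowing the arm.* The immediate PROMPTS offer makes this plausible, but no section says what enumerators know. It remains an inference.

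**Conclusion.** The point holds as an error in the sample-size section. Section 16.2 applies a post-allocation, one-arm event to the number followed in every facility, conflicts with sections 5.4 and 5.7, and reports 58 where its stated factors give 72 and the follow-up plan implies about 90.

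For the planned cohort, the as-randomized MDE is about 6.2 points, not 7. Expressed as an effect among PROMPTS users at 80% uptake, it is about 7.7 points. Which of these should be set against the 7 points depends on what the 7 points was meant to be, and the protocol does not say. The results rest on the ICC of 0.01, 75% tracking and the design values carried over from the quality-of-care calculation; the two user-effect figures also assume no effect in non-acceptors. The protocol does not establish that the planned comparison is selected or that the trial is underpowered.

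**What to change.** In sections 16.1 and 16.2:

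1. State that the postnatal-care comparison includes every consented woman according to her facility's allocation.
2. Remove the 80% from the sample count, and reconcile the 58 with sections 5.4 and 5.7: about 90 followed per facility at 75% tracking.
3. State the number of facilities per arm, alpha, sidedness and power for this outcome.
4. Restate the MDE: about 6.2 points as randomized, equal to about 7.7 points among users at 80% uptake if non-acceptors gain nothing. Report about 72% power for a 7-point effect confined to users.
5. Say whether the 7 points was meant as the difference between arms or the effect among users.

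This costs a few sentences and no change to data collection. If the 7 points was meant as a user effect, the stated power becomes less favourable.

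An optional safeguard is to ask women in both arms, before the arm is disclosed, whether they would accept text messages. Any later analysis of acceptors would then have a matching control group, and enumerators' possible knowledge of the arm would not affect the answer. It costs one extra baseline question and a slight delay in PROMPTS sign-up.

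### The 6.88-point detectable effect for quality of care carries no small-cluster correction; with 20 facilities per arm it is about 7.1 points, or 78% power at 6.88

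*Protocol*

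**What the plan says.** Section 16.2 bases the endline sample size on the quality-of-care index from observed deliveries, the primary health worker outcome. Its inputs are:

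- a control mean: "we assume that average quality of care for the control group will be 0.58";
- a spread: "with a standard deviation of 0.13";
- clustering: "Assuming an intra-cluster correlation (ICC) of 0.35";
- size and error rates: "a cluster size of 100 patients, 20 clusters per arm, alpha of 0.05, and power of 0.80".

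The result is that "the minimum detectable impact would be 6.88 percentage point increase in quality of care or an 11.9% increase in the quality-of-care index". The section does not say whether the test is one- or two-sided, which reference distribution was used, or whether the small number of clusters was allowed for.

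Section 5.1 states that "Randomization of the intervention package will occur at the facility level" and allows 40 to 50 facilities in total. Sections 3.2 and 5.4 speak of about 40. Section 16.1 plans t-tests and multiple regression, without further detail.

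**The concern.** The usual design-effect formula with normal quantiles treats the standard error as known. In a trial randomised by facility, the standard error of the arm difference is estimated mainly from the scatter of facility means, and here there are 40 of them. With so few, the reference distribution is t on the number of facilities minus 2, and the same effect yields somewhat less power. If this was not allowed for, the detectable effect is stated a little too favourably. Because Section 16.2 gives it to two decimals as what this design detects at 80% power, even a small correction changes the printed figure.

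**Working it through.** **Inputs (all from Section 16.2).** SD 0.13, read as the total SD; ICC 0.35; m = 100 deliveries per facility; k = 20 facilities per arm; alpha 0.05; power 0.80; control mean 0.58.

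**1. Standard error.**
- Design effect = 1 + (100 − 1) × 0.35 = 35.65.
- SE = 0.13 × sqrt(2 × 35.65 / (20 × 100)) = 0.13 × sqrt(0.03565) = 0.02455, or 2.455 points.

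**2. The protocol's figure.**
- Two-sided, normal quantiles: (1.960 + 0.842) × 2.455 = 6.88 points; 6.88 / 58 = 11.9%. Both stated numbers reproduce.
- One-sided, normal quantiles: 6.10 points, so a two-sided test was evidently used.
- t with patient-level degrees of freedom, 2 × 20 × 100 − 2 = 3,998: also 6.88. The stated figure therefore corresponds to normal quantiles or to degrees of freedom that count patients.

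**3. Which degrees of freedom apply.**
- The variance of a facility mean is proportional to ICC + (1 − ICC)/m = 0.35 + 0.65/100 = 0.3565.
- The between-facility share is 0.35 / 0.3565 = 98%. This is a share of the variance of a facility mean. Of the total variance of individual scores, only 35% is between facilities.
- An unadjusted comparison thus rests on 40 facility means, with 2 × 20 − 2 = 38 degrees of freedom.

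**4. The figure with 38 degrees of freedom.**
- (2.0244 + 0.8512) × 2.455 = 7.06 points. The noncentral t distribution gives the same 7.06.
- Relative to control: 7.06 / 58 = 12.2%.
- Power at 6.88 points: 0.780 by noncentral t, and 0.780 in a simulation of t-tests on facility means.
- Shortfall: 7.06 − 6.88 = 0.18 points, or 0.18 / 6.88 = 2.6% of the stated effect; 80% − 78% = 2 points of power.

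**5. What would change it (noncentral t, 80% power).**

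| Facilities per arm | Deliveries per facility | Detectable effect (points) |
|---|---|---|
| 20 | 100 | 7.06 |
| 20 | 120 (Section 5.4) | 7.05 |
| 21 | 100 | 6.88 |
| 25 | 100 | 6.28 |

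More deliveries per facility barely help, because the facility is the limiting unit. One more facility per arm restores the stated figure.

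**The case against.** The strongest reply is that this is a refinement of a planning approximation. The stated figure follows exactly from its inputs by a standard formula, and the correction is smaller than the uncertainty in those inputs. With t on 38 degrees of freedom, an ICC of 0.33 in place of 0.35 gives 6.86 points, and an SD of 0.1266 in place of 0.13 gives 6.87. Section 5.1 also permits up to 50 facilities, and 42 are enough. All of this stands, and it keeps the point minor. It does not make 6.88 the 80%-power effect for "20 clusters per arm, alpha of 0.05, and power of 0.80", which is the design that Section 16.2 names; the larger number of facilities is permitted, not promised.

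A reader might infer more than the protocol supports:

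- **An arithmetic error.** There is none; step 2 reproduces both stated numbers.
- **Final tests against 1.96.** With 40 clusters that would raise the type I error to about 5.7%. But the protocol nowhere plans it: Section 16.1 names t-tests and regression, and the degrees of freedom for the final tests can properly be left to the statistical analysis plan.
- **A further loss from county terms.** The protocol states neither stratification by county nor county terms. Counting their lost degrees of freedom without the variance they might explain would be one-sided.
- **The same fault in the postnatal-care figure.** The correction moves it from 6.96 to 7.14 points, and both round to the 7 points stated.

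**Conclusion.** The point holds as a minor correction. For 20 facilities per arm, Section 16.2's inputs give a detectable effect of about 7.1 points (7.06; 12.2% of 0.58) at 80% power, or about 78% power at 6.88 points. The result rests on a two-sided test at 0.05, 0.13 as the total SD, equal cluster sizes, and an unadjusted comparison. Covariate adjustment could lower the detectable effect and unequal facility volumes could raise it; the protocol quantifies neither. The finding does not show that the trial is materially underpowered or that its planned analysis is invalid.

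**What to change.** In Section 16.2, make one of these changes:

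- for 20 facilities per arm, restate the detectable effect as about 7.1 points (12.2%) at 80% power, from t quantiles on 38 degrees of freedom;
- keep 6.88 points and state the power as 78%;
- keep 6.88 points at 80% power and say that it holds with 21 facilities per arm.

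Either of the first two costs one sentence and no patients, and the figure becomes slightly less favourable. The third is honest only if at least 42 facilities are enrolled: two more than the calculation assumes, within the range in Section 5.1, but with the fieldwork of two further sites and a matching edit to the count of about 40 in Sections 3.2 and 5.4.
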